**2.14 What is the likely rate of loss to follow up?**

Loss to follow up during the school year was 5% in previous studies, although they did not include a

follow-up measurement 9 months later, which is remarquably low for the field (115). We will allow for an additional moving rate of approximately 4% and an additional drop-out rate of 3% (estimated on the basis of previous studies), giving a total rate of loss to follow up of around 12% at T2.

**2.15 How many centers will be involved?**

This is not a multicentric study. The five high schools are involved in partnership with one university

hospital (McGill University Health Centre – MUHC). The involved high schools are big institutions (up to 2000 students) belonging to francophone school boards, because these are the schools designed to welcome the newly arrived immigrants and refugees to Montréal (Law 101). On the Island of Montréal, there are a total of 27 public francophone high schools (including those in non multiethnic neighborhoods). Our sample corresponds to 20% of all francophone high schools and to around 50% of

high schools in highly multiethnic neighborhoods. The participating schools are situated geographically in different parts of the Montréal Island, although all are in socio-economically deprived areas. Three of the high schools are among the poorest on the Island (Saint-Henri, Lucien-Pagé and La Dauversière) while the two others have a mixed population profile, in that they welcome children from middle class families in their gifted programs (Saint-Luc and Saint-Exupéry) but also serve extremely poor neighborhoods (for example, the Walkley area in the case of Saint-Luc).Thus, these schools are very representative of Montréal’s multiethnic high schools (see table 1 describing the socio-demographic and cultural profile of the participating schools).

**2.16 Data analysis**

The effects of theatre intervention on the primary outcome, SDQ Impairment Impact Supplement, will

be assessed by comparing the average change in SDQ of children at the end of the 12-week intervention period in children in the theatre intervention to the children in the control group. The average change in SDQ of children in the theatre group will also be compared to the average change in SDQ for children in the tutorship group. These analyses will be performed using a linear mixed effects model (also called a hierarchical model), which will appropriately account for the within-classroom correlation of children. In addition to a term for the intervention group, the linear mixed effects model will also adjust for child age and gender.

Analyses of secondary outcomes will also be carried out using linear mixed effects models; these outcomes are: (a) change in impairment, self-rated at T2 (b) change in SDQ Global Scores, self-rated (c) change in SDQ Global Scores, teacher-rated (d) change in impairment, teacher rated (e) change in Adolescent Friendship Inventory (AFI) (f) change in School Performance. Analysis of the group x time interaction will be performed with the repeated measures (T0, T1, T2). All analyses will be conducted using the **R** statistical programming language, using the lme procedure to fit the linear mixed effects models.

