**2.11 What is the proposed sample size?**

Ten classes per condition will be included in the study, with an estimated 18 students per class. Power

calculations were performed assuming: 1) a compliance rate of 80%; 2) 5% loss to follow-up at the end of the twelve-week program (T1); 3) within-class variance and residual variance estimated from the pilot data.

Power calculations were performed via simulation, using the above parameters and assuming a Normal distribution of change in SDQ scores over a range of possible effect sizes. Accounting for the within- class clustering of children using a linear mixed effects model with a random effect for class and a fixed effect for the intervention, the proposed sample size has 77.5% power to detect a moderate effect size (d

= 0.50), and 84.5% power to detect a 5 point difference in SDQ score between the theatre intervention and the control group. In the pilot study, there was a mean difference in change on the SDQ of 5.85 points between the intervention and control groups. However, the study participants were newly arrived immigrant and refugee youth who had been undergoing recent intensive stress. The type of symptoms tends to decrease relatively rapidly with time, even if the interactions significantly helped them to subside (113). In the present study, we will be working with youth presenting emotional and behavioural difficulties for a relatively long time, since this prompted their inclusion in special class. We thus expect that these chronic problems, although possibly more severe, may be more difficult to shift. Studies of psychosocial interventions are typically powered based on a moderate effect size (e.g., d = 0.50) to represent clinically significant change (e.g., (114)), Depression: management of depression in primary and secondary care. Clinical practice guideline No. 23. London: National Institute for Clinical Excellence). Thus, the study was powered to achieve at least a moderate (d =.50) effect size which corresponds to a 3.95 change in the SDQ impairment score.

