**2.18 Sub group analyses**

Analyses to determine the effect of gender and age will be conducted. In the pilot study, however, there

were no differential effects of treatment in the pilot study based on sex (p = .95) or age (p = .96). Thus, although we will control for a potential effect, we do not expect it to be significant. If classes and schools differ significantly on measured socio-demographic variables describing socio-economic and cultural variables we will include them as covariates in the outcome analysis to control for variation between groups/schools.

**2.19 Pilot studies:** The first and larger pilot study was done on regular and welcoming classes. No quantitative data was obtained in the subsequent piloting of the project in special class (90). Other pilot was recently realized (at the request of Québec Ministry of education) in special classes of under- schooled youth (n = 55). In these classes, the majority of youth have suffered high exposure to trauma and separation. This pilot results confirmed that self-report impairment decreased significantly with the intervention and that the intervention appeared to be more beneficial when exposure to premigratory hardship is high (89).

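### The primary change-score model omits the T0 impairment score: valid, but less precise than a T0-adjusted model and sensitive to chance T0 differences between 10 classes per arm

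*Protocol*

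**What the plan says.** Section 2.16 defines the primary comparison as "comparing the average change in SDQ of children at the end of the 12-week intervention" period, in theatre against control classes, using a linear mixed model that accounts for correlation within classrooms. It then names the model terms: "In addition to a term for the intervention group, the linear mixed effects model will also adjust for child age and gender". The T0 score is not listed.

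Three other places bear on this:

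- Section 2.18 allows further covariates, but only socio-demographic variables on which classes and schools differ significantly: "we will include them as covariates in the outcome analysis to control for variation between groups/schools". The T0 outcome score is not one of these.
- Section 2.16 also plans a group-by-time analysis of T0, T1 and T2, placed after the secondary outcomes. It is not described as adjusting for baseline or constraining it to be equal across arms. With free T0 means, its T0–T1 contrast is again a difference in change.
- Section 2.11 bases power on simulated change scores, with a random class effect and a fixed intervention effect. The design size is stated there: "Ten classes per condition will be included in the study, with an estimated 18 students per class".

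Sections 2.7 and 2.8/2.9 show that the T0 values of the outcomes are collected.

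**The concern.** The T0 value of the outcome is likely to be the most prognostic variable available, and the model leaves it out while including age and gender. Subtracting T0 from T1 is a form of baseline adjustment, but with the slope fixed at 1. With equal variances at the two times, the efficient slope is rho. Two things follow whenever rho is below 1:

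- The treatment estimate has a larger variance than it needs.
- If the arms differ at T0 by chance, the estimate moves by about (1 − rho) times that difference, in the opposite direction (regression to the mean).

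Both matter here because only 10 classes per arm are randomised and the stated power at the target effect is already below 80%. The same form of analysis is planned for secondary outcomes (a) to (f).

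**Working it through.** **Inputs from the protocol (section 2.11).** 10 classes per arm; 18 students per class; 80% participation; 5% loss by T1. This gives 18 × 0.80 = 14.4 students per class at T0 and 14.4 × 0.95 = 13.68 at T1. The target is d = 0.50 = 3.95 points, so the implied SD is 3.95/0.50 = 7.9, taken here as the SD of change. Stated power is 77.5% at 3.95 points and 84.5% at 5 points.

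**Assumed, not given.** Two-sided 5% test; T0–T1 correlation rho of 0.3 to 0.8; equal variances at T0 and T1; the ICC.

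**1. The stated power.** SE = SD × √[(2/10) × (ICC + (1 − ICC)/13.68)].

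- 77.5% at 3.95 points needs 3.95/SE = 1.960 + 0.755 = 2.715, so SE = 1.45. With SD 7.9 this corresponds to an ICC of about 0.104 (normal approximation; 0.085 with 18 df). The same SE gives 93.0% at 5 points, not 84.5%.
- 84.5% at 5 points needs SE = 1.68, an ICC of about 0.14 to 0.165. That SE gives only 65.2% at 3.95 points.

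No single variance reproduces both figures. The 77.5% is used below as an anchor only.

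**2. Precision.** Var(change) = 2σ²(1 − rho). The residual variance after adjusting for T0 is σ²(1 − rho²). The ratio of adjusted to change is (1 + rho)/2.

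Power at 3.95 points, starting from 77.5%:

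| rho | ratio | class and student variance both shrink | only student-level variance shrinks |
|---|---|---|---|
| 0.3 | 0.65 | 92.0% | 83.1% |
| 0.5 | 0.75 | 88.0% | 81.5% |
| 0.7 | 0.85 | 83.8% | 79.9% |
| 0.8 | 0.90 | 81.7% | 79.1% |

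Example for column three, rho 0.5: 2.715/√0.75 = 3.135, and 3.135 − 1.960 = 1.175, which gives 88.0%. Example for column four, rho 0.8, ICC 0.104: SE = 7.9 × √[0.2 × (0.104 + 0.90 × 0.896/13.68)] = 1.426, and 3.95/1.426 − 1.960 = 0.81, which gives 79.1%.

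The gain runs from 79.1 − 77.5 = 1.6 points to 92.0 − 77.5 = 14.5 points. Anchored instead on the 84.5% figure, power at 3.95 points starts at 65.2% and rises to about 70% (rho 0.8) to 83% (rho 0.3) if both variance levels shrink.

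A mixed-model simulation of one setting (ICC 0.14, rho 0.3, 14 per class, 250 runs) gave 68.8% power for change and 82.4% with T0 as covariate. It used the same correlation at class and student level, which is the favourable case.

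**3. Chance T0 difference between arms.** In units of the T0 SD, its standard deviation is √[(2/10) × (ICC + (1 − ICC)/14.4)], where the ICC is that of the T0 score:

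- ICC 0.05: 0.15 (95% range ±0.30)
- ICC 0.10: 0.18 (±0.35)
- ICC 0.20: 0.23 (±0.44)

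At ICC 0.10 and rho 0.5, a difference of one standard deviation shifts the change-score estimate by 0.5 × 0.18 = 0.09 SD. At rho 0.5 the SD of change equals the SD of the score, so this can be set against d = 0.50: 0.09/0.50 = 18%. A difference at the edge of the 95% range shifts it by about 0.18 SD. These are upper figures, because the formula ignores the stratification by school.

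**The case against.** **The analysis is coherent and valid.** The primary hypothesis in section 1.2 concerns a greater reduction from T0 to T1, and both the power simulation and the analysis use change. Classes are assigned at random within school, so the change-score contrast is unbiased over randomisations. This stands in full. A reader might infer that the trial's estimate is biased, or that T0 imbalance goes uncorrected. The protocol supports neither: change already subtracts T0, and the shift is conditional on the imbalance that happens to occur.

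**The covariate list may not be complete.** A full list is often settled in the analysis plan, which is not shown. This stands only in part. The protocol names both the response and the covariates, and section 2.18 extends the list only to socio-demographic variables.

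**T0 adjustment does not fully remove imbalance in a clustered design.** At ICC 0.10, the class-level part is 0.10 of 0.10 + 0.90/14.4 = 0.1625, about 62% of the imbalance variance. One student-level covariate corrects that part fully only if the between-class and within-class slopes are equal. This stands.

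**The sizes are soft.** Rho, the ICC and equal variances are assumptions, and the 77.5% anchor conflicts with the 84.5%. Section 2.3 takes two classes per arm from each of five schools, so any between-school part of the T0 variance is balanced by design. This stands and limits the claim about size. It does not change its direction: the gain disappears only as rho approaches 1.

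**Conclusion.** The point holds as a matter of precision and of bias conditional on chance imbalance, not of validity. Section 2.16 names group, age and gender, omits T0, and so fixes the baseline slope at 1. Under the stated assumptions, T0 adjustment would add roughly 2 to 15 points to the stated 77.5% power. The lower end applies when rho is 0.8 and only student-level variance shrinks.

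A reader might take the table to promise power of 82% to 92%. The protocol does not support that, because its two power figures imply different variances and it gives neither rho nor the ICC. The chance T0 difference has a standard deviation of at most about 0.15 to 0.23 SD for ICC 0.05 to 0.20, of which the change score passes on (1 − rho). I am confident of the textual reading and the direction, and much less so of the size.

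**What to change.** In section 2.16, add the student's T0 value of the outcome as a covariate in the linear mixed model for the primary outcome and for each secondary outcome (a) to (f). The group coefficient is then the same whether the response is written as the follow-up score or as change, so the hypothesis of greater reduction can keep its wording. Keep the unadjusted mean change by arm as a descriptive summary.

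State that this reduces the effect of class-level baseline imbalance but need not remove it.

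The cost is one covariate that is already collected and a line of text, with no new data and no further classes.

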**1.2 Principal research questions to be addressed:**

**Aim:** To evaluate the efficacy of a school based theatre intervention program for immigrant and refugee

youth in special classes in improving mental health and academic outcomes.

**Primary hypothesis:** Students in the theatre intervention group will report a greater reduction in

impairment from symptoms (emotional and behavioural) compared to students in the control groups from pre-intervention (T0) to the end of the 12-week intervention program (T1).

**Secondary hypothesis #1:** Students in theatre intervention group will report a greater reduction in impairment compared to student in the control groups from T0 to T2.

**Secondary hypothesis #2:** Students in theatre intervention group will report a greater reduction in impairment compared to students in the tutoring group from T0 to T1 and T2.

**Secondary hypothesis #3:** Compared to students in the tutoring and control groups, students who received the theatre program intervention will report a greater decrease in global emotional and behavioural symptoms as reported by themselves and by their teachers from T0 to T1 and T2.

**Secondary hypothesis #4:** Compared to students in the tutoring and control groups, students who received the theatre program intervention will report a greater reduction in impairment (teacher reported) from T0 to T1 and T2.

**Secondary hypothesis #5**: Compared to students in the tutoring and control groups, students who received the theatre program intervention will report a greater increase in the quality of peer relationships from T0 to T1 and T2.

**Secondary hypothesis #6**: Compared to students in the control groups, students who received the theatre program or the tutoring intervention will report a greater improvement in school performance.

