**2.4 What are the proposed methods for protecting against other sources of bias?**

The questionnaires will be filled in by the students themselves in class and by teachers who are not the

homeroom teachers. The teachers who fill in the questionnaires for each student will thus not be present in class with the students for the activity. Even if it cannot be guaranteed that these teachers will be blind to the experimental or control status of the students, given that the students can comment on their activities, they will not be involved in the activities. Lastly, educational achievement is an unbiased source of evaluation, as school marks are given by several different teachers and therefore do not depend solely on the teacher who is in attendance during the activity. At T2, all the teachers involved will be completely blind to the experimental status of the youth. Contamination is another possible bias. The theatre intervention is however quite complex and in our experience has never been implemented spontaneously by teachers who were willing to try it, after discussing with their colleagues. In the case of the tutoring intervention, the added manpower (two resource teachers) is something every teacher in special class would wish to have, but cannot implement independently.

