**2.7 What is the proposed frequency and duration of follow-up?**

Data on the evaluation of the effects of the theatre expression workshops on the students will be

gathered pre- and post-intervention, as well as at follow-up nine months after the end of the intervention. Whenever feasible, the evaluation of the maintenance of the effect of psychosocial interventions for some time (classically 6 months) after termination is a good indicator of their efficacy (34, 36). In the present case, a six month follow up would have resulted in a T2 measure in September, at the beginning of the next school year. This would not have enabled us to assess the medium term effect of the intervention on school performance because the first report card is in November. Furthermore, the teachers’ report Strength and Difficulties Questionnaire (SDQ) is more valid when teachers have been working with the youth for a few months. For these reasons we decided that T2 would be taking place at the beginning of December, 9 months after the end of the intervention. The evaluation questionnaires for each measurement time will be filled in during a 90-minute class period and will be designed so that students with learning difficulties can complete them in approximately 45 minutes. Theoretically all the students taking part will have another school year to finish (high school graduation is at the end of grade 11 in Quebec). However, the youth older than 16 years old who present behavioural and academic difficulties are more at risk to drop out of school than their peers. Nonetheless, in our past studies, the losses attributable to follow-up during a school year have been minimal (< 5%). We therefore do not expect a significant attrition at T2. Special measures will be taken to keep contact with the students who may leave the school at the end of academic school year. Families, who have recently immigrated, are quite mobile. To address potential attrition linked to moving, youth will be asked at T1 if they plan to remain in the same school and/or to move and if so, what is the name of their future school and/or there

new address. Permission to contact them in the future will be requested and contact information for the student will be obtained.

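### Teacher-rated outcomes at T2 are analysed as change from T0 although the T2 rater is probably a different teacher, which adds avoidable noise of unknown size to the teacher part of secondary hypothesis 3 and to hypothesis 4

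*Protocol*

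**What the plan says.** Section 1.2 states secondary hypothesis 3 for symptoms "as reported by themselves and by their teachers from T0 to T1 and T2", and hypothesis 4 for teacher-reported impairment over the same intervals. Section 2.16 lists the matching outcomes as "c) change in SDQ Global Scores, teacher-rated (d) change in impairment, teacher rated", analysed with linear mixed models. For the primary analysis it says that "the linear mixed effects model will also adjust for child age and gender". It names no baseline score and no rater term for any outcome. The power section (2.11) describes the model as "using a linear mixed effects model with a random effect for class and a fixed effect for the intervention".

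On who rates, section 2.4 assigns the teacher questionnaires to teachers other than the homeroom teacher: "The teachers who fill in the questionnaires for each student will thus not be present in class with the students for the activity". It grants that these teachers may learn the arm, then says "At T2, all the teachers involved will be completely blind to the experimental status of the youth". Section 2.7 fixes that "T2 would be taking place at the beginning of December, 9 months after the end of the intervention", partly because the teacher SDQ "is more valid when teachers have been working with the youth for a few months". The number of raters per class is not given, and the change of rater is not discussed.

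**The concern.** A change score removes a rater's personal leniency only if the same rater scores both times. From T0 to T1, within one school year, that can hold. From T0 to T2 it probably does not, so the score mixes pupil change with a difference between two teachers. As an illustration, an unchanged pupil scored 18 by a strict teacher and 12 by a lenient one shows a 6-point improvement.

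If one teacher rates a whole class at T0, every pupil in it carries the same error. More pupils per class cannot average that out; only more classes can. Section 1.3/1.4 gives durability of effect as a reason for the trial, and section 2.4 presents the T2 teachers as fully blind. A null teacher-rated result at T2 caused by rater noise could therefore be read as the effect having faded.

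**Working it through.** **Is the T2 rater new?** Three statements point the same way. T2 falls in the next school year. The date was set partly to give teachers a few months with the youth, which matters mainly if they are new to them. Blinding is not guaranteed for the earlier raters but is called complete at T2. This is a strong inference, not a stated fact.

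**The plan's own figure.** The 77.5% in section 2.11 is for theatre versus control with T1 losses. No power is stated for any teacher-rated or T2 outcome. Pupils per class are 18 × 0.80 × 0.95 = 13.68 at T1 and 18 × 0.80 × 0.88 = 12.67 at T2 (about 127 per arm). The class variance is not printed, so 77.5% cannot be rebuilt directly. It corresponds to an intraclass correlation of about 0.085: SE = √(2 × [0.085 + 0.915/13.68]/10) = 0.174 SD, and t with 18 df gives about 77.5% at d = 0.50.

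**Model for the class mean** (variances as shares of the score variance without raters; all assumed):
- true class C = 0.05, stable pupil P = 0.55, error E = 0.40
- rater L = 0.10, k raters per class
- class-by-time variance T = 0 or 0.08
- m = 13 pupils, two-sided 5% level

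Variance of the mean change, same rater: 2E/m + T.

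Variance of the mean change, new rater: L/k + R2 + 2E/m + T. Here R2 is about L/m if pupils are remixed among T2 teachers, and L/k if classes stay intact.

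Variance of the T2 mean adjusted for the T0 class mean: V2 − (C + P/m)²/V0, with V0 = C + P/m + L/k + E/m and V2 = C + P/m + R2 + E/m + T.

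SE = √(2 × variance/10), multiplied by √(18/17) for the estimated covariate. Power uses the noncentral t with 18 df (change) or 17 df (adjusted).

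**Worked case: one T0 rater, remixed, T = 0**
- Same rater: 0.80/13 = 0.0615; SE 0.111; power 99%.
- Change, new rater: 0.10 + 0.0077 + 0.0615 = 0.1692; SE 0.184; power 73%.
- Adjusted: C + P/m = 0.0923, V0 = 0.2231, V2 = 0.1308. Variance = 0.1308 − 0.0923²/0.2231 = 0.0926; SE 0.140; power 92%.

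Simulated trials give 69% v 87%. The closed form is a little optimistic because it treats T2 raters as independent from pupil to pupil.

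**Power at d = 0.50 and 10% rater variance, change v adjusted**

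| Setting | Closed form | Simulation |
|---|---|---|
| One rater, remixed | 73% v 92% | 69% v 87% |
| One rater, intact | 54% v 66% | 53% v 65% |
| Three raters, remixed | 91% v 96% | 88% v 93% |
| Three raters, intact | 84% v 89% | 83% v 89% |
| One rater, remixed, T = 0.08 | 56% v 69% | 55% v 66% |
| One rater, intact, T = 0.08 | 44% v 51% | 45% v 52% |
| Three raters, remixed, T = 0.08 | 70% v 74% | 65% v 69% |
| Three raters, intact, T = 0.08 | 64% v 67% | 65% v 68% |
| Three raters, remixed, T = 0.08, C = 0.25 | 70% v 70% | 73% v 72% |
| Three raters, intact, T = 0.08, C = 0.25 | 64% v 64% | 72% v 70% |

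The two columns differ in level in the last rows, but neither shows a gain. T = 0.08 brings power without rater variance to about 80%, close to the plan's planning level.

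**Other rater variances** (one rater per class, T = 0, simulated): at 5%, 86% v 94% remixed and 75% v 82% intact; at 20%, 46% v 76% and 34% v 47%.

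**Price if there is no rater variance.** With C = 0.25 and T = 0.08 the closed form gives 80% v 78.5%.

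**Bias.** With d = 0 and 20% rater variance, the change analysis rejected in 4.6% of simulated trials, so the type I error holds.

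**The case against.** The strongest reply is that nothing stated is wrong. Classes are randomised, so rater differences average out between arms, and the class random effect carries the extra variance. The outcomes are secondary and no power is claimed for them. Section 2.4 speaks of teachers in the plural and gives no number per class. With several raters the shared error shrinks, and with large true class differences the change score already does most of what adjustment would do. In section 2.16 only the self-rated impairment item names T2. The teacher items name no time point, and the group-by-time analysis could be parameterised in a statistical analysis plan that is not shown.

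Most of this stands, and it limits the point. It does not remove it. Section 1.2 names T2 for both hypotheses, and section 2.16 defines the outcomes as change. A repeated-measures T0-T2 contrast that leaves baseline unadjusted has the same weakness.

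A reader might infer more than the documents support:
- That leniency certainly acts as a whole-class error. This needs one T0 rater per class, which is not stated.
- That the T2 teacher comparison is biased. Randomisation prevents that.
- That the 77.5% or the primary analysis is affected. Both rest on self-report, where the same pupil answers each time.
- That T0-T1 teacher change is affected too. That holds only if raters change within the year.

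**Conclusion.** The point holds as one of avoidable imprecision. The plan appears to count on new teachers at T2 for blinding, yet analyses the T0-T2 difference as if the rater were constant. The scope is the teacher-rated half of hypothesis 3 and hypothesis 4, at T2 only.

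The size cannot be fixed from the documents, which give neither rater variance nor raters per class. At an assumed 10% rater variance and d = 0.50, the gain from adjustment runs from about 0 points (three raters per class, large true class differences) to about 18 points (one rater per class, pupils remixed at T2). Once class-by-time variance brings reference power to about 80%, with class differences kept at 5%, it is about 3 to 12 points. Adjustment removes only part of the T0 rater's contribution; the T2 rater's own leniency stays in any analysis of T2 scores. The change is worth making because it costs little, not because a large loss has been shown.

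**What to change.** In section 2.16, for the two teacher-rated outcomes at T2, take the T2 teacher score as the outcome. Enter the T0 teacher score as two covariates: the mean of the pupil's T0 class and the pupil's deviation from that mean. The split matters because rater leniency sits in the class mean when one teacher rates the class. Keep the random effect for the randomised class and keep all pupils in the analysis.

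Record a coded rater identifier on every teacher form, collected prospectively. Use a random effect for the T2 rater only as a sensitivity analysis, and only where raters and classes are not confounded; with intact classes and one T2 rater each, the two cannot be separated. Do not restrict the T0-T1 analysis to pupils rated by the same teacher twice, because that selects after randomisation.

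State in section 2.8/2.9 that T0-T2 teacher results compare different raters, so a null result there is not by itself evidence that the effect faded.

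Cost: a few lines of text and one field on the form. The analysis spends one class-level degree of freedom (about 1-2 points of power if there is no rater variance) and reports an adjusted difference in place of a mean change. It needs no extra pupils, visits or staff.
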